### **2.2.2 Economic assessments**

- 6) Length of hospitalization;
- 7) All costs during hospitalization;
- 8) All costs after the surgery;

## **3. Study design**

### **3.1 Type of this study**

This is a single-centre, prospective, randomized, controlled study.

## **3.2 Eligibility criteria**

We will consecutively recruit adult patients who are undergoing CABG (on-pump/off-pump) and agree to participate in this clinical trial.

### **3.2.1 Inclusion criteria**

- 1) Adult patients scheduled for isolated CABG.
- 2) Patients who are willing to participate in this study and sign the informed consent.

### **3.2.2 Exclusion criteria**

- 1) age < 18;
- 2) emergent CABG;
- 3) history of cardiac surgery;
- 4) simultaneously undergoing any other cardiac surgery (such as Morrow procedure, valvular surgery, ventricular reconstruction due to ventricular aneurysm, or repair of the congenital heart diseases);
- 5) critical condition requiring hemodynamic support before CABG, such as need for extracorporeal membrane oxygenation or intra-aortic balloon pump;
- 6) history of AF;
- 7) receiving antiarrhythmic therapies except of taking beta-blockers last 2 weeks before surgery.

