### **6.2 Data collection at enrollment**

Adult patients scheduled for isolated CABG will be screened for eligibility. Patients who meet the eligibility criteria and willing to give written informed consent will be

invited to participate. At this period, following baseline characteristics will be collected:

- 1) Age, sex, height, weight, medical history, family history and physical examination;
- 2) Comprehensive laboratory tests and examinations: blood, biochemistry, coagulation, biomarkers, transthoracic echocardiography, peripheral artery/vein ultrasound, chest radiography, ECG, entire aorta CT, lung function/chest CT/head CT/cardiac MR (if necessary);
- 3) Coronary artery evaluation according to coronary angiogram, including atherosclerotic sites and stenosis degree;
- 4) Other comorbidities and concomitant medications.

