## **2. Study objective**

### **2.1 Primary objective**

The primary outcome is POAF in 6 days, defined as a supraventricular arrhythmia lasting for >30 seconds. Patients will be monitored continuously beginning within one hour after the surgery to the 6th day postoperatively through the NS-SP-B-01 Attached Dynamic ECG Recording System. In addition, the overall lasting time of supraventricular arrhythmia will also be recorded for evaluating AF burden. Heart

rates will be continuously monitored, including lowest/highest/average heart beats, premature atrial/ventricular contractions etc. Two independent and blinded research doctors will interpret the ECG and determine the existence of POAF.

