## **6. Statistical test for primary endpoint**

### **6.1 Statistical analysis method**

The primary endpoint is the POAF incidence in 6 days after surgery. For the primary

outcome, results will be compared as categorical variable and according to the approach mentioned in 4.2. As sensitivity analysis of the primary outcome, the time-to-event analysis will be performed with Kaplan-Meier survival curves and compared by the log-rank test. In addition, the AF episodes, AF burden, lowest/highest/average heart beats and premature atrial contractions will also be compared by approach mentioned in 4.2. Unless otherwise stated, statistical significance level is set to 0.05 (2-sided).

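### The rhythm-history exclusion names AF only, while the primary event is any supraventricular arrhythmia over 30 seconds with no new-onset condition, so some pre-existing arrhythmias can enter and be counted as events

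*Supplement*

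**What the plan says.** The latest protocol (version 2.0, section 4.2) and the latest SAP (section 3.2.2) have the same seven exclusions. Two concern rhythm:

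- Item 6 is "6) history of AF".
- Item 7 is "receiving antiarrhythmic therapies except of taking beta-blockers last 2 weeks before surgery".

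The event is set in section 2.1 of both documents: "The primary outcome is POAF in 6 days, defined as a supraventricular arrhythmia lasting for >30 seconds". Recording starts within one hour of surgery and runs to postoperative day 6. On adjudication the same section says: "Two independent and blinded research doctors will interpret the ECG and determine the existence of POAF". It gives the readers no rule for a rhythm that was present before surgery.

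Protocol 6.2 collects the information that would identify such patients. The baseline list includes "Age, sex, height, weight, medical history, family history and physical examination", and the examinations include "chest radiography, ECG, entire aorta CT". No entry criterion requires sinus rhythm on that ECG. Earlier supraventricular arrhythmia is neither a minimization factor (SAP 3.6.1) nor a subgroup (SAP 7), and no analysis uses it.

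**The concern.** A prevention trial should enrol patients who are free of the event at baseline, or require the event to be new. Here the rhythms screened out by history (AF) are narrower than the rhythms counted (any supraventricular arrhythmia over 30 seconds). The gap consists of patients with atrial flutter, atrial tachycardia or another supraventricular tachycardia, past or ongoing, who are untreated or take only a beta-blocker. Item 6 does not name their rhythm and item 7 exempts their drug.

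Such a patient could meet the event definition as soon as recording begins. The result would then include recurrences of an old arrhythmia, reported as failures of prevention. Events that the procedure does not avert raise the rate in both arms, pull the risk ratio towards 1 and cost some power.

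**Working it through.** **1. Does another provision close the gap?**

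| Provision | Effect on a patient with earlier flutter or other SVT |
|---|---|
| Item 6 | Not excluded; only AF is named |
| Item 7 | Excluded if on an antiarrhythmic other than a beta-blocker in the last 2 weeks; otherwise not |
| Enrolment ECG and history | Recorded, but neither decides entry |
| Section 2.1 definition | Counts the rhythm if it lasts over 30 seconds; no new-onset condition |
| Blinded adjudication | Applies the same definition; no written rule to discount an old rhythm |

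The gap is narrowed by item 7 but not closed.

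**2. The plan's own figure.** Protocol 8.2 and SAP 3.5 give 23% in controls, a 50% reduction, 80% power, alpha 0.05 and 408 patients, raised to 430 for 5% loss. The usual two-proportion formula with 23% against exactly 11.5% gives 338 in total, or 372 with continuity correction. Rounding 11.5% to 12% and applying the correction gives exactly 408, and 408/0.95 = 429.5, so 430. The documents do not state that this was the method. It explains why 204 per arm gives more than 80% power at 23% against 11.5% with an uncorrected chi-squared test.

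**3. Dilution model.** The inputs from the plan are p = 0.23 (control) and 0.115 (denervation), 204 per arm, and two-sided 0.05. Two inputs are assumptions, because the documents give neither:

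- f, the share of entrants with such a history: 1% to 5%;
- r, their probability of recurrence within 6 days: 50% to 100%, the same in both arms.

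A patient in this group has an event if the old rhythm recurs or, failing that, at the ordinary risk p. The arm's event rate is then

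rate = (1 − f)p + f[1 − (1 − p)(1 − r)] = p + f·r·(1 − p).

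Only the product f·r matters, and the absolute difference shrinks by the factor (1 − f·r).

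Power = Φ{[d√n − 1.96√(2p̄(1 − p̄))] / √(p₁(1 − p₁) + p₂(1 − p₂))}, with d = p₁ − p₂ and p̄ their mean.

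With no such patients: [0.115 × 14.283 − 1.96 × 0.5343] / 0.5281 = 1.127, so power is 87.0%.

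For f = 5% and r = 100%:

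- control: 0.23 + 0.05 × 0.77 = 0.2685;
- denervation: 0.115 + 0.05 × 0.885 = 0.1593.

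| f | r | Control | Denervation | Risk ratio | Power, 204 per arm |
|---|---|---|---|---|---|
| 0 | – | 23.0% | 11.5% | 0.50 | 87.0% |
| 1% | 50% | 23.4% | 11.9% | 0.51 | 86.1% |
| 1% | 100% | 23.8% | 12.4% | 0.52 | 85.1% |
| 3% | 50% | 24.2% | 12.8% | 0.53 | 84.1% |
| 3% | 100% | 25.3% | 14.2% | 0.56 | 81.0% |
| 5% | 50% | 24.9% | 13.7% | 0.55 | 82.1% |
| 5% | 100% | 26.9% | 15.9% | 0.59 | 77.0% |

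Power passes below 80% only when f·r exceeds about 3.5%. In the extreme row the absolute difference is 11.5 × 0.95 = 10.9 points, and the extra events expected are 204 × 0.0385 = 7.9 in controls and 204 × 0.0443 = 9.0 with denervation.

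**4. How far this depends on the test.** The headroom above 80% belongs to 11.5% and the uncorrected test. On the basis that reproduces 408 (12%, with d reduced by 1/n for continuity), power starts at 80.0% and falls to 78.9% at f·r = 0.5% and 68.7% at f·r = 5%. The loss is about 1 to 11 points, against 1 to 10 points in the table.

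**5. Type I error.** If the procedure has no effect, p is equal in both arms, and so is p + f·r·(1 − p). The test's level is unchanged.

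**The case against.** The strongest reply is that the mismatch comes from loose wording of the endpoint, not from the entry criteria. The stated hypothesis is prevention of POAF, and for that a history of AF is the natural exclusion. Elsewhere the plan treats AF as the target: monitoring is for AF (SAP 3.3), AF episodes and burden are compared (SAP 6.1), and arrhythmias other than AF form a separate safety outcome (SAP 2.2.1). If section 2.1 were narrowed to AF, most of this point would go. That stands, and the fix allows for it. But the definition in section 2.1 is the only written event rule, and if flutter stays in the endpoint the gap stays too.

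A second reply is that the model is a worst case. It assumes that the procedure does nothing for recurrences of the old rhythm, whereas the rationale (SAP 1.3) describes the ligament of Marshall and adjacent atrium as origins of arrhythmias, so the procedure might act on some of them. Nothing in the documents suggests that 5% of entrants would be affected or that all would recur. That also stands.

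Three stronger readings might be inferred, and the documents support none of them:

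- **AF is the only rhythm problem screened at entry.** Item 7 removes part of the group as well.
- **The comparison is biased towards one arm, or false positives are more likely.** Allocation is randomized and the same definition is read blind in both arms, so the extra events are expected equally.
- **The trial is underpowered for this reason.** With no prevalence in the documents that cannot be shown, and on the table's basis it would take nearly the extreme case.

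**Conclusion.** The point holds, as a minor one. Item 6 is narrower than the event in section 2.1, item 7 closes only part of the gap, and nothing requires the event to be new. The expected result is non-differential dilution, and some events would not mean what the trial takes them to mean. The validity of the test is not affected.

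The figures in the table illustrate the size and do not estimate it. They rest on an assumed prevalence and recurrence, on the plan's 23% and 50% reduction, and on no effect of the procedure on recurrence. The more secure ground for acting is interpretation: as written, the recurrence of a known arrhythmia counts as a failure to prevent a postoperative one.

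**What to change.** Reconcile item 6 in protocol 4.2 and SAP 3.2.2 with section 2.1, so that the excluded history, and the excluded rhythm on the enrolment ECG, are the rhythms counted as events. If section 2.1 keeps its present breadth, item 6 should cover AF, atrial flutter and other supraventricular arrhythmia of the kind counted. If section 2.1 is narrowed to AF, or to AF and flutter, item 6 should match that.

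For patients already enrolled, keep the intention-to-treat primary analysis in SAP 5.1 and 6.1 unchanged. Prespecify one sensitivity analysis, before unblinding, that repeats it without patients who have a recorded history of a counted supraventricular arrhythmia or such a rhythm on the baseline ECG. Report the number of such patients by arm.

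The cost is a short amendment and one extra analysis from data that protocol 6.2 already collects. A few candidates would be lost, at a centre that reports about 5,000 isolated CABG operations a year.

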### 3.3 Overall study design and participants' timeline

During the primary screening, patients will be evaluated for the eligibility into the study, and an individual informed consent will be signed at the willingness of each patient. Then, participants will be randomly allocated to either intervention or control group. After surgery, monitoring for the occurrence of AF will be lasted until the 6th day postoperatively among all of the patients. Meanwhile, complications such as pericardial effusion will also be assessed. On the day of discharge, participants will be investigated by 12-lead standard ECG and echocardiogram. During the 30-day follow-up, information such as the participants' overall health status, medication use, and whether they have experienced any kind of arrhythmia or MACCEs, will be collected. The participants will also be investigated by ECG and echocardiogram again for further assessment (**Figure 1**).

[figure not shown]

**Figure 1. The study flow Chart.**

### **3.4 Partial cardiac denervation procedure**

In the intervention group, participant will undergo partial cardiac denervation through cutting off the LOM and resecting the fat pad along the Waterston groove. Specifically, during the on-pump CABG, the heart will be pulled to the right to expose the LOM between the left atrial appendage and the left pulmonary veins under extracorporeal circulation, and the LOM will be cut off by electrotome. Then, the fat pad along the Waterston groove will be exposed between the right pulmonary veins and right atrium and excised completely to the surface of myocardium, with the upper edge extending beyond the opening of the right upper pulmonary vein and the lower edge to the inferior vena cava. For off-pump CABG, we will cut off the LOM in the same way mentioned above. Then if the patient's heart is well tolerated and hemodynamics is stable, a fixator can be used to fix the heart when resecting the fat pad along the Waterston groove. Otherwise, cardiac denervation will be performed after CABG is completed. The estimated additional surgery time is 5 minutes. In order to achieve a satisfactory efficacy, a thorough cardiac denervation to myocardium surface will be emphasized. In addition, the existence of ganglia will be further proved through histologic analysis using the fat pad samples collected from 10 pairs of patients with or without POAF, respectively.

### **3.5 Sample size justification**

Two parallel arms will be required. The occurrence of POAF after cardiac surgery was about 23%, according to the prior study. Based on a detailed reviewing of the existing

studies, cardiac denervation reduces the incidence of POAF by 50%. Therefore, with 80% power and 0.05 alpha, 408 participants are needed to detect 23% POAF rate in the control group and a reduction by 50% in the intervention group. Taking into account a 5% protocol violation rate and patient loss/dropout, a population size of 430 (215 in each group) shall be sufficient for this investigation. As one of the world's largest centers of cardiovascular diseases, Fuwai Hospital completes more than 10 thousand cardiac surgeries every year, of which an approximate of 5 thousand are isolated CABG. This trial shall be completed in due course.

### **3.6 Randomization and blinding**

#### **3.6.1 Randomization after subjects enrolled**

A controlled, randomized process will be used to assign participants to treatment groups. A computer-generated minimized random allocation technique based on factors including age, sex, history of myocardial infarction, and left ventricular ejection fraction will be employed to ensure that the cases are distributed equally. The department research fellow will inform the surgeon of the patient's group assignment once they are under general anesthesia in the operating room.

#### **3.6.2 Blinding**

As different surgical operations are involved, complete double-blindness cannot be achieved. In order to reduce the researcher bias, surgeons are not allowed to know the result of patient's assignment until surgery, and the third-party supervisor responsible

for randomization shall inform the surgeons of the results only after general anesthesia and before the surgical procedure starts. Patients and data analysts will be blinded throughout the process. Unblinding will be done under the third-party supervision after all data analysis is completed.

## **4. Descriptive analyses**

### **4.1 Study flow chart of the study**

A CONSORT flow diagram will be presented showing the numbers of patients screened, randomized, received surgery (with details), and followed up after discharge.

### **4.2 Baseline comparability of randomized groups**

Demographic and clinical characteristics of patients at baseline will be presented by randomised group. Number of subjects, mean, standard deviation, median, interquartile range (IQR), minimum, and maximum will be used for description of continuous variables. Continuous variables will be tested by Student's t test if normally distributed; otherwise, by the Mann-Whitney U test. Counts and percentages will be used to summarize the categorical variables. Chi-squared test or Fisher's exact test will be applied for categorical variables, as appropriate.

Intraoperative data such as number of grafts, % off pump, % saphenous vein/radial artery, duration of operation will also be presented.

## **5. Patient groups for analysis of outcomes**

### **5.1 Effectiveness**

The main analyses will be conducted on all randomized patients, applying the principle of intention to treat (ITT), as far as is practically possible, except where specified. The only reason for excluding patients will be the absence of outcome information. All patients randomized will be analysed in the groups assigned at randomization, irrespective of subsequent management and events. Thus any patients deemed ineligible following randomization will not be removed from the trial if this information became available after randomization and thus after disclosure of the allocation.

### **5.2 Safety**

In the analysis of safety/harms patients will be analysed both by ITT and according to the operation received (i.e. per-protocol). Only patients who received the surgical procedure to which they were randomly allocated will be included in the per protocol analysis of safety data.

## **6. Statistical test for primary endpoint**

### **6.1 Statistical analysis method**

The primary endpoint is the POAF incidence in 6 days after surgery. For the primary

outcome, results will be compared as categorical variable and according to the approach mentioned in 4.2. As sensitivity analysis of the primary outcome, the time-to-event analysis will be performed with Kaplan-Meier survival curves and compared by the log-rank test. In addition, the AF episodes, AF burden, lowest/highest/average heart beats and premature atrial contractions will also be compared by approach mentioned in 4.2. Unless otherwise stated, statistical significance level is set to 0.05 (2-sided).

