## **7. Subgroup analysis for the primary outcome**

Subgroup analysis will be conducted based on the risk factors of POAF reported by previous studies as follows: sex, age ( $\geq 65$  years vs.  $< 65$  years), LVEF ( $> 55\%$  vs.  $\leq 55\%$ ), body mass index ( $\geq 25$  kg/m^2 vs.  $< 25$  kg/m^2), left atrium size ( $\geq 40$  mm vs.  $< 40$  mm), and history of myocardial infarction, diabetes mellitus and hypertension.

To test for a differential effect of randomized treatment across subgroups, an interaction term (treatment group by subgroup) will be fitted in the Cox proportional hazards model. If proportional hazards cannot be assumed a multiple logistic regression model will be fitted.

Subgroup analyses will be conducted only with respect to the primary outcome.

Treatment effect in each subgroup shall be presented along with the P value for the interaction term in the model.

All patients randomized shall be included in the analysis, irrespective of whether surgery was undertaken.

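### The primary test ignores the four minimisation factors and names no effect measure, and subgroup effects may be reported on a different scale from the primary comparison

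*Supplement*

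**What the plan says.** SAP 3.6.1 (and protocol 5.2) allocates patients by "A computer-generated minimized random allocation technique based on factors including age, sex, history of myocardial infarction, and left ventricular ejection fraction". SAP 7 chooses its subgroup factors because earlier work links them to POAF. All four minimisation factors are on that list, with body mass index, left atrial size, diabetes and hypertension.

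SAP 6.1 states: "The primary endpoint is the POAF incidence in 6 days after surgery". For the comparison it says "results will be compared as categorical variable and according to the approach mentioned in 4.2". Section 4.2 is the section on baseline comparability, and its rule is "Chi-squared test or Fisher's exact test will be applied for categorical variables, as appropriate". Protocol 8.1 names the same tests. The one sensitivity analysis of the primary outcome in SAP 6.1 is unadjusted as written: "the time-to-event analysis will be performed with Kaplan-Meier survival curves and compared by the log-rank test". Section 4.2 offers counts and percentages as summaries. No risk difference, risk ratio, odds ratio or confidence interval is named for the primary comparison in either document.

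For subgroups, SAP 7 says that "an interaction term (treatment group by subgroup) will be fitted in the Cox proportional hazards model", and then: "If proportional hazards cannot be assumed a multiple logistic regression model will be fitted". It does not say how proportional hazards will be judged, whether the switch is made once or factor by factor, or which covariates enter the logistic model.

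**The concern.** Three gaps meet in the analysis of one endpoint.

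- **The design is not reflected in the test.** Minimisation on prognostic factors reduces the chance imbalance between arms. An unadjusted test computes its standard error as if that imbalance could still occur. The reported standard error of a difference in proportions is then somewhat too large, and some power is given away.
- **The primary estimate is not fixed.** Only a test is specified, so the headline effect measure and its interval could be chosen after the results are known.
- **The subgroup scale is left to the data.** Interaction depends on scale. A Cox model gives hazard ratios, the fallback gives odds ratios, and the primary comparison is of 6-day proportions. SAP 7 requires the effect in each subgroup to be presented, so this will appear in the report.

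**Working it through.** **Inputs from the plan (SAP 3.5, 6.1):** control risk 23%; 50% relative reduction, so 11.5%; two-sided alpha 0.05; 80% power; 408 patients before loss (204 per arm), 430 after.

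**The plan's own figure.** With p̄ = 0.1725, the pooled formula is n per arm = [1.960·√(2·0.1725·0.8275) + 0.842·√(0.23·0.77 + 0.115·0.885)]² / 0.115² = (1.047 + 0.444)² / 0.013225 ≈ 168.2. That rounds up to 169 per arm, 338 in total, or 372 with continuity correction. The stated 408 is not reproduced from these inputs. This is a separate matter, and it means only that the trial is larger than its inputs require. By the normal approximation, power for 23% against 11.5% is about 87% at 204 per arm and 89% at 215. The step from 408 to 430 does reproduce: 408/0.95 = 429.5, rounded up.

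**What adjustment gains.** The documents give no prevalences, covariate effects, minimisation cut-points or allocation probability. All are assumed here: age ≥65 in 45%, female 22%, prior MI 25%, low LVEF 25%, and a biased coin of 0.8. In each scenario 5,000 trials of 408 patients were simulated. The unadjusted chi-squared test and the treatment term of a logistic model with the four factors (as binary variables) were applied to the same trials.

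The variance of a standardised risk difference relative to the unadjusted one is [v − ½·Var(r₀ + r₁)] / v. Here v = 0.1771 + 0.1018 = 0.2789, and r₀ and r₁ are a patient's risks under control and intervention.

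| Assumed odds ratios (age, sex, MI, LVEF) | Type I error, unadjusted → adjusted | Power, unadjusted → adjusted | Variance ratio | Adjusted N matching 408 unadjusted |
|---|---|---|---|---|
| 1 / 1 / 1 / 1 | 5.5% → 5.5% | 87.5% → 87.4% | 1 | 408 |
| 1.5 / 1.2 / 1.2 / 1.2 | 5.0% → 5.0% | 87.5% → 87.7% | 0.99 | 405 |
| 2.5 / 1.3 / 1.3 / 1.5 | 4.5% → 5.0% | 87.9% → 88.8% | 0.96 | 393 |
| 4 / 1.5 / 1.5 / 2 | 4.1% → 5.1% | 88.6% → 90.2% | 0.92 | 375 |

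The Monte Carlo standard error of the type I error rates is about 0.3 points. In interval terms, the unadjusted 95% half-width at the planned rates is 1.96·√(0.2789/204) ≈ 7.2 percentage points. In the strongest scenario it becomes 7.2·√0.918 ≈ 6.9.

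A second simulation used 430 patients, a coin of 0.85 and 3,000 trials per scenario, with moderate and strong effects (c-statistic 0.64 to 0.70). Power rose from 89.1% to 89.7% and from 89.0% to 90.4% at the planned effect. If the true reduction is 40% (13.8%), it rose from 69.9% to 71.3% and from 70.7% to 73.2%.

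**How far the scales differ.** At the planned rates:

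- risk ratio = 0.115/0.23 = 0.50
- hazard ratio = ln(0.885)/ln(0.77) = 0.47, under proportional hazards and complete 6-day follow-up
- odds ratio = (0.115/0.885)/(0.23/0.77) = 0.435

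SAP 1.1 quotes POAF incidence after CABG of 5% to 40%. Take these as illustrative extremes and halve the risk at each. The risk ratio is 0.50 at both ends. The odds ratio moves from (0.025/0.975)/(0.05/0.95) = 0.49 to (0.20/0.80)/(0.40/0.60) = 0.375. The hazard ratio moves from ln(0.975)/ln(0.95) = 0.49 to ln(0.80)/ln(0.60) = 0.44. The same uniform halving is therefore no interaction on one scale and some interaction on another.

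**The case against.** The case for leaving the plan alone is considerable. The chi-squared test is valid, its type I error is not inflated, and power already exceeds 80% under the plan's assumptions. The gain from adjustment rests wholly on assumed covariate effects and vanishes if those effects are nil or mild. The Cox model is consistent with the plan's own time-to-event sensitivity analysis, and the logistic fallback models the same binary endpoint. All of this stands, and it keeps the point modest.

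Three stronger readings are tempting, and the documents do not support them.

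- A reader might infer that ignoring the minimisation factors makes the primary p-value unsafe. The simulations show the opposite direction: the unadjusted test is, if anything, conservative.
- A reader might infer that adjustment would narrow the interval for any effect measure. For an odds ratio it raises power but does not narrow the interval on the log-odds scale. The precision gain belongs to a standardised risk difference or risk ratio.
- A reader might infer that subgroup results could not be read against the primary result at all. At the planned rates the three ratios are 0.50, 0.47 and 0.435, with the same direction and similar size. A table mixing hazard and odds ratios is possible but not certain, because SAP 7 does not say whether the switch is global or per factor.

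The objection does not answer the missing effect measure and interval, or the undefined switching rule. Neither depends on how prognostic the factors are.

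**Conclusion.** The point holds as a low-cost improvement that should be made; it does not threaten the validity of the trial. The primary analysis omits four factors that the plan balances by design and regards as prognostic. The price is 0 to about 1.6 points of power at the planned effect (1 to 8% of the variance of a risk difference), with an unadjusted type I error down to about 4.1% in the strongest scenario. Those sizes depend on assumed prevalences and odds ratios and on binary coding of the factors. The simulated adjusted test was the logistic treatment term, so the p-value of the standardised risk difference itself was not simulated.

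The absence of a named effect measure with a confidence interval, and the data-driven choice between Cox and logistic models, follow from the text alone and need no assumption.

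**What to change.** **SAP 6.1 and protocol 8.1, changed together so that they agree.** The primary analysis is a logistic regression of 6-day POAF on arm, age, sex, history of MI and LVEF. It is standardised over all analysed patients to one named primary measure: the adjusted risk difference, with its 95% CI and p-value. The adjusted risk ratio with 95% CI is secondary, and the chi-squared test is kept as supportive. State how age and LVEF enter the model (continuous is the natural choice) and how the standard error is obtained.

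**SAP 7.** Test every treatment-by-subgroup interaction in this same binary model and delete the Cox-then-logistic rule. Present each subgroup effect on the scale of the primary measure, with its interval, and say on which scale the interaction p-value is computed.

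**Cost.** Wording in two documents, agreed before unblinding, and a few lines of code. Age, sex, medical history and echocardiography are already collected at enrolment (protocol 6.2). Sample size, conduct and patient procedures do not change.
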